#### Implementation outcomes analyses

To assess fidelity of the blood pressure assessment protocol (*primary implementation outcome*) we will examine the difference in percent of patient-visits with recorded blood pressure (1 = blood pressure measured; 0 = blood pressure not measured) between intervention and control clinics using mixed effects log-binomial regression. If the mixed effects log-binomial model fails to converge, we will use a generalized estimating equation (GEE) log-binomial model with exchangeable correlation structure and robust standard errors; if the GEE log-binomial fails to converge, we will use a GEE log-Poisson model [39, 40]. We will examine changes in blood pressure assessment between clusters (“horizontal”) and across periods (“vertical”) to evaluate heterogeneity in treatment effects by cluster and period, respectively. Between-cluster and between-period heterogeneity will be evaluated through an intervention by clinic interaction term.

Adaptation data recorded during the active intervention period will be examined using means and standard deviations (or median [IQR] if data are skewed) and frequency counts with percentages. Maintenance of blood pressure assessment by clinic staff will be examined by adding an interaction term between intervention exposure status (control vs. intervention) and implementation phase (i.e., research staff vs. clinic staff) to the model described for the primary implementation outcome. Means and standard deviations (or median IQR) will be used to summarize normalization process questionnaire [32] data at the beginning and the end of the maintenance period. Paired samples t-tests (or Wilcoxon rank-sum tests) will be used to compare normalization questionnaire scores at the beginning and the end of the maintenance period.

Exploratory analyses will examine exposure to the implementation strategies (e.g., > 80% of audit and feedback sessions received) and compare blood pressure assessment rates against that of clinics with lower exposure via the modeling approach for dichotomous outcomes previously described. Causal diagrams and latent variable modeling will also be considered as exploratory tools to examine mechanisms through which implementation strategies affect blood pressure assessment implementation.

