The allocation sequence began with an observation period where none of the clinics had neither received the implementation strategies nor rolled out the patient intervention (Period 1). In this period, we collected implementation and clinical data under the control condition. After the control period, clinics crossed-over to the intervention condition, three at a time based on their randomization sequence. To date, all nine clinics have-crossed over to the active intervention period which will run from study months 4–15 (Periods 2–5). Since this intervention was randomized at the clinic level and involves providing clinical care, blinding was not possible. For each step, clinics were notified one month in advance prior to initiation of the intervention.

At month 14, all clinics will initiate a two-month offboarding transition period (Period 5). Here, research staff will support clinic staff to ensure that implementation strategies continue to be executed, while also helping them to further integrate the blood pressure assessment protocol within routine care. From months 16–27, research staff will be withdrawn from clinics and a maintenance observation period will begin (see Table 1).

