**EFFECTIVENESS EVALUATION**		
**Outcome definitions**	**Time points**	**Data source**
***Reach*** Percentage and representativeness of patients with elevated blood pressure and HIV that receive the intervention	At the initial / enrollment study visit (months 1–15)	• Study REDCAP form • Medical charts
***Effectiveness*** Primary clinical outcome: difference in mean systolic BP between the intervention and control periods	All visits in months 1–15, excluding the two months following intervention initiation	• Medical charts
***Cost-effectiveness*** Health utility of the intervention and direct medical costs of additional patient visits and/or hospitalizations	Control, active intervention (months 1–15), and maintenance periods (months 16–27)	• Quality of life (EQ-5D) patient questionnaire • Patient-reported cost survey • Study records
***Patient-level Maintenance*** Extent to which blood pressure improvements observed during the intervention phase are maintained	Active intervention (months 4–15) and maintenance (months 16–27) periods	• Medical charts • Study REDCAP form

*BP* blood pressure

*Adoption* will be determined as the percentage and representativeness of clinics that complete the blood pressure assessment protocol at the initial study step (i.e., did they roll out intervention? Yes/No). Intervention fidelity (*primary implementation outcome*) will be defined as the difference in percentage of patient visits with recorded blood pressure measurement between intervention and control periods. We will also keep track of adaptations made to the blood pressure assessment protocol via care coordinator notes and reports. Clinic-level *maintenance* of the intervention will be defined as the extent to which blood pressure continues to be assessed after the active intervention period ends based on medical chart reviews. We will also assess the normalization of the blood pressure assessment protocol using a 23-item questionnaire [32] healthcare workers will complete at the beginning and at the end of the maintenance period.

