### Statistical methods

#### Overview

The statistical analyses are described according to implementation outcomes derived from clinics (i.e., *adoption*,* implementation*, and *maintenance* of the blood pressure assessment protocol) and outcomes related to intervention impact (i.e., *reach*,* effectiveness*, and *effect maintenance* of the intervention). We will use the standard Hussey and Hughes model for analysis of stepped-wedge designs [38] which includes fixed effects for both interventions and time periods, and a random effect for sites. We will extend this model to account for non-normal outcomes, repeated measurements on participants, and to include key covariates for each RE-AIM outcome as described below. All outcomes, patient characteristics, and clinic characteristics will be summarized (both overall and by intervention status) using means and standard deviations for continuous variables (or median [IQR] if data are skewed) and frequency counts with percentages for categorical variables. Statistical differences between pre- and post-intervention and initiated versus delayed (control) clinics during each observation period will be examined. Contingent on the observed distributions, differences in categorical outcomes will be assessed using chi-square or Fisher’s exact tests, and differences in continuous variables will be tested using independent group t-tests or Wilcoxon rank-sum tests. *P*-values < 0.05 will be considered statistically significant. Following these analyses, the costing, cost-effectiveness, and budget impact analysis will be conducted and are described at the end of this section.

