Similar to the analyses described for the implementation outcome, we will evaluate treatment heterogeneity between clusters (“horizontal”) and across periods (“vertical”). Additional subgroup analyses will evaluate treatment-effect heterogeneity by prior treatment for hypertension, HIV regimen, CD4 count, viral load, age, sex, and immigration status. We will present subgroup analyses with *P*-values from interaction tests as well as estimates of mean differences and 95% confidence intervals. In exploratory analyses, we will use a longitudinal cohort approach restricted to patients with two or more visits and with moderate-to-severe hypertension (i.e., systolic blood pressure > 160 mmHg or diastolic blood pressure > 100 mmHg) during the active intervention period. We will apply linear or logistic models, contingent on the distribution of the outcome, following the approach described for the primary implementation outcome analyses.

To assess *maintenance* of clinical effects, we will determine if the blood pressure improvements observed during the active intervention phase (research staff implementation, months 4–15) differ from those observed in the maintenance phase (clinic staff implementation, months 16–27). For this, we will use the same linear mixed model described for the primary effectiveness outcome and estimate the mean difference in systolic blood pressure between active intervention and maintenance periods. Results will be presented as a mean difference and 95% confidence intervals. If the mean is higher in the maintenance period and the 95% CI does not overlap zero, we will conclude that the improvements on systolic blood pressure were not maintained.

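### The clinic-level maintenance interaction cannot be estimated, and the patient-level maintenance contrast is confounded with calendar time and judged against zero rather than a tolerable loss

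*Protocol article*

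**What the plan says.** The base model for all outcomes is the Hussey and Hughes model, "which includes fixed effects for both interventions and time periods, and a random effect for sites" (Protocol article, Overview of the statistical methods).

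For clinic-level maintenance, the plan takes the primary fidelity model and proposes "adding an interaction term between intervention exposure status (control vs. intervention) and implementation phase (i.e., research staff vs. clinic staff") (Implementation outcomes analyses). The outcome is the extent to which blood pressure "continues to be assessed after the active intervention period ends based on medical chart reviews" (Outcome measures and definitions, text below Table 3).

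For patient-level maintenance, "we will use the same linear mixed model described for the primary effectiveness outcome and estimate the mean difference in systolic blood pressure" between the active and maintenance periods (Effectiveness outcomes analyses). The stated aim is to see whether the improvements of the active phase differ from those of the maintenance phase. The conclusion that they were not maintained is drawn as follows: "If the mean is higher in the maintenance period and the 95% CI does not overlap zero".

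The Study design section fixes the timing. Clinics moved in sequence: "clinics crossed-over to the intervention condition, three at a time based on their randomization sequence". On completion it says: "To date, all nine clinics have-crossed over to the active intervention period which will run from study months 4–15 (Periods 2–5"). On the next phase it says: "From months 16–27, research staff will be withdrawn from clinics and a maintenance observation period will begin".

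**The concern.** An exposure-by-phase interaction needs all four combinations of control or intervention with research-staff or clinic-staff delivery. The design supplies three. No clinic is under control in months 16–27, and every clinic changes phase in the same month, so phase is a function of calendar time alone, and calendar time already has its own fixed effects.

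For the clinic-level outcome, the named coefficient does not exist in the data. Software faced with such a model drops a column or reports a number that depends on which column it drops. If a maintenance-period effect is dropped instead of the interaction, the output labelled as the interaction is an adjusted change from Period 1 to that period.

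For the patient-level outcome the contrast can be calculated, but the plan reads it as evidence on whether the effect over control was kept. The data cannot show that. The decision rule adds a second problem. It asks whether a rise is statistically detectable, not how much of the gain has gone, so the verdict follows the standard error.

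**Working it through.** **Inputs.** Nine clinics in three sequences of three, Periods 1–5 in months 1–15, all clinics crossed over, and research staff withdrawn everywhere for months 16–27 (Study design). Fixed effects for intervention and period, random effect for site (Overview). Target difference 5 mmHg, SD 20 mmHg, and an average of 184 patients per clinic per year (Sample size calculation). The protocol gives no figure for the maintenance analyses, so there is none to reproduce.

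**1. Clinic-level interaction.** On the link scale, for clinic i in period j, the model is

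α_i + β_j + θX_ij + δX_ijM_j,

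where X is intervention status and M = 1 in maintenance. In every maintenance cell X = 1, so XM = M. M equals the sum of the maintenance-period indicators, so any δ can be absorbed into the β_j of those periods.

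A rank check with clinics as fixed effects shows this:

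| Maintenance periods | Base model: columns / rank | Plus interaction | Plus phase and interaction |
|---|---|---|---|
| 1 | 15 / 15 | 16 / 15 | 17 / 15 |
| 4 | 18 / 18 | 19 / 18 | 20 / 18 |
| 12 | 26 / 26 | 27 / 26 | 28 / 26 |

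A monthly layout without the two months after initiation, assuming crossovers at months 4, 7 and 10 because Table 1 is not shown, gives 36 / 36, 37 / 36 and 38 / 36. The added rank is zero each time. Treating site as random changes nothing: with a common intercept and one maintenance period the ranks are 7 / 7, 8 / 7 and 9 / 7. The GEE fallback models use the same fixed-effect columns. Removing the period effects does not restore a true interaction either: intercept, exposure, phase and interaction are 4 columns of rank 3, because one cell is empty.

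**2. Patient-level contrast.** Under intervention, the maintenance mean minus the active mean is a difference of averaged β_j, since θ cancels. An estimability check on the base model confirms that this contrast can be estimated, while a separate phase coefficient cannot.

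If Δ is the secular change and δ the change in effect, the contrast identifies only Δ + δ. A contrast of zero fits Δ = 0 with δ = 0 (all of the gain kept). It fits Δ = −5 with δ = +5 mmHg (all of the gain lost) equally well.

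**3. Decision rule.** Take SE = 20 × √(2/n) for n readings per phase, ignoring clustering and repeated measures. The smallest observed rise called not maintained is 1.96 × SE. The chance that a true rise d is flagged is Φ(d/SE − 1.96).

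| n per phase | SE (mmHg) | Smallest rise flagged (mmHg) | Chance that a true 2.5 mmHg rise is flagged | Chance that a true 5 mmHg rise (complete loss) is flagged |
|---|---|---|---|---|
| 100 | 2.83 | 5.54 | 14% | 42% |
| 200 | 2.00 | 3.92 | 24% | 71% |
| 400 | 1.41 | 2.77 | 42% | 94% |
| 1656 (184 × 9) | 0.70 | 1.36 | 95% | about 100% |

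At n = 1656 the threshold is 1.36 / 5 = 27% of the target, so a result that keeps about 73% of it is called not maintained. If the variance is inflated by the protocol's design effect of 3.2, purely as illustration because that factor was derived for the treatment contrast, the threshold becomes 1.36 × √3.2 ≈ 2.4 mmHg, about half the target.

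**The case against.** **The period layout is not visible.** The text numbers only Periods 1–5, and Table 1 is not shown. If only those five periods have indicators, the model with the interaction has 15 columns and rank 15, so a coefficient can be computed. That is correct, but the term is then simply the maintenance-period effect. It still equals the phase indicator, is still confounded with calendar time, and is not an interaction.

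**The blood pressure analysis specifies no phase term.** This stands. A reader might infer that both maintenance analyses are inestimable. The documents do not support that: the patient-level text asks for a mean difference, and that can be estimated as a contrast of period effects. Its weakness is confounding with time.

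**The comparator and the data source look unsafe but are largely covered.** Months 4–15 include control months for clinics that cross later. However, the primary effectiveness model classifies data by clinic status at measurement and censors the first two months after initiation, and the maintenance analysis inherits that model. Likewise, a reader might infer that triage-room forms will be compared with charts. Table 3 lists medical charts as a source for both fidelity and clinic-level maintenance, so a like-for-like comparison is available. Wording could make both points explicit; neither is an error.

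**The rule is modest.** The plan reports the mean difference with its 95% interval, so the size of any loss is visible. It never says that a non-significant rise proves maintenance, and that stronger reading should not be attributed to it. What remains is that the only stated verdict rests on a comparison with zero.

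**The illustrations are rough.** They treat readings as independent, and the true precision of the contrast is unknown. They show how the rule depends on precision; they do not predict the trial's result.

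**Conclusion.** The clinic-level interaction cannot be estimated in a model with effects for the maintenance periods, and it is not a true interaction in any layout consistent with the Study design section. This rests on two stated facts: all nine clinics have crossed over, and research staff leave all of them for months 16–27.

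The patient-level contrast can be computed, but it identifies only the sum of secular change and change in effect. It therefore cannot show whether the improvement over control was kept. Its rule yields a verdict that depends on precision: under SD 20 and independence, the smallest rise flagged runs from 1.36 mmHg at 1656 readings per phase to 5.54 mmHg at 100.

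The point is a should-fix. Both outcomes are secondary, and neither co-primary analysis uses months 16–27, so the main results are not affected.

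**What to change.** 1. Drop the exposure-by-phase interaction. For both outcomes, classify clinic-months as control, research-staff intervention or clinic-staff intervention, and compare clinic-staff months with post-transition research-staff months.
2. Estimate that comparison as a contrast of period effects. As a sensitivity analysis, replace the period effects with an explicitly stated parametric time trend. With a linear trend, the model with clinic effects and three-level status is identified (12 columns, rank 12). That identification comes from the assumed trend, which the data cannot verify.
3. Label the result an uncontrolled before-after comparison, confounded with calendar time.
4. For the clinic-level outcome, use chart-recorded blood pressure measurement in both phases.
5. For systolic pressure, have the investigators choose a tolerable loss before the maintenance data are analysed, for example a stated fraction of 5 mmHg. Conclude maintained if the 95% interval for the rise lies below it, not maintained if it lies above, and inconclusive if it spans it.

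The cost is a change of analysis wording, with no new data. The price is a maintenance claim that is openly weaker than the present text suggests, and a third possible outcome, inconclusive.

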### Implementation strategies

The implementation strategies used in this study aim to promote fidelity to the hypertension detection and treatment protocol recommended by the South African Hypertension Society Guidelines [26]. The implementation strategies were designed through community-engaged formative work that was guided by the Behavior Change Wheel [27]. Details and results from our formative work are reported elsewhere [21]. Briefly, we conducted interviews with relevant actors (patients, clinicians, and administrators) to identify barriers to detecting and treating elevated blood pressure (for healthcare workers), or to managing it (for patients). The barriers identified were reviewed and ranked by the study’s Community Advisory Board and a final set of barriers to be addressed in the study was selected. These barriers were then mapped onto relevant intervention functions and behavior change techniques specified in the Behavior Change Wheel [27].

Four implementation strategies resulted from our formative work: identify and prepare care champions, change record systems, conduct ongoing training, and audit and provide feedback. Because blood pressure assessment equipment was lacking in participating clinics, a fifth implementation strategy was added –changing the physical structure and equipment. The five implementation strategies tested in this study are described in Table 2. These were defined using Expert Recommendations for Implementing Change [28] and specified according to established recommendations [29]. The implementation strategies will be carried out by the study care coordinator during the active intervention period. During the maintenance period, the care coordinator will be withdrawn, and the implementation strategies will be carried out by clinic staff.

**Table 2 Tab2:** Implementation strategy specification

Name	Specification^a^ (actor, action, target)	Temporality and dose
Identify and prepare care champions	Care coordinator recruited and trained to assist healthcare workers with implementation of the elevated blood pressure detection and treatment protocol.	Throughout active intervention period

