**IMPLEMENTATION EVALUATION**		
**Outcome definitions **	**Time points**	**Data source**
***Adoption*** Participation rate and representativeness of clinics that initiate the blood pressure assessment intervention	At every initial study step (i.e., just the initial rollout step)	• Study REDCAP form
***Implementation Fidelity*** Primary implementation outcome: extent to which the BP measurement protocol is implemented	All clinic visits in months 1–15, excluding the two months following intervention initiation (during research staff implementation phase)	• Medical charts • Study REDCAP form • Adaptations recorded by care coordinator / research staff
***Cost*** Initial costs of implementation strategies and cost of implementing the BP measurement protocol	Control, intervention (months 1–15) and maintenance (months 16–27) periods	• Study records • Time and motion assessment
***Clinic-level Maintenance*** Extent to which BP continues to be measured and is normalized after active intervention period	Months 16–27 (during clinic staff implementation)	• Medical charts • Healthcare worker normalization questionnaire

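### Normalization is a clinic-level outcome, but its first-named test is paired and covers only staff who stayed; the named alternative covers all respondents, so the choice of test also changes the population

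*Protocol article*

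**What the plan says.** Table 3 of the protocol article defines clinic-level maintenance as "Extent to which BP continues to be measured and is normalized after active intervention period", over months 16–27, with medical charts and a healthcare worker normalization questionnaire as sources. The text under Outcome measures and definitions describes a 23-item questionnaire that "healthcare workers will complete at the beginning and at the end of the maintenance period". It does not say whether the respondents are a fixed group of workers or whoever is in post at each time.

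Study design sets the interval: "From months 16–27, research staff will be withdrawn from clinics and a maintenance observation period will begin". Under Implementation strategies, in that period "the care coordinator will be withdrawn, and the implementation strategies will be carried out by clinic staff".

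Implementation outcomes analyses has two sentences on the questionnaire. The first is descriptive: "Means and standard deviations (or median IQR) will be used to summarize normalization process questionnaire" data at both ends of the period, with no restriction to workers who have both forms. The second names the test: "Paired samples t-tests (or Wilcoxon rank-sum tests) will be used to compare normalization questionnaire scores" between those two times. Nothing is said about workers with only one questionnaire.

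**The concern.** The outcome belongs to the clinic: has the protocol remained normal practice there a year after research support ended? A paired t-test answers a different question, namely whether the individuals present at both times changed their scores. Workers who left and workers who joined contribute nothing to it.

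Joiners matter here. Table 2 places coordinator-led training and feedback in the active intervention period, so a worker who arrives in months 16–27 never had them from the coordinator. Whether the protocol survives a change of staff is part of what maintenance means, and the first-named test sets those staff aside.

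The alternative in brackets does not resolve this. The rank-sum test compares independent groups, and the article uses it that way in the Overview of Statistical methods and in the reach analysis, beside the independent-groups t-test. Read literally, a decision prompted by the shape of the score distribution would also change whose scores are compared. The formal result could be no change among stayers while the descriptive means fall, with no rule for which of the two is the normalization result.

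**Working it through.** The article gives no staff number, SD, correlation, turnover or power for this questionnaire, so there is no stated figure to reproduce. The checks below use assumed values.

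**Inputs from the article.** Interval: months 16 to 27, i.e. 12 months. Clinics: nine. Tests: paired t-test or rank-sum.

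**Assumptions.** N respondents at each time with common SD s. A share q have both questionnaires, so 1 − q of end-of-period staff are new. Within-worker correlation is r. Stayers do not change, leavers resemble stayers, and joiners score d SD lower. Clinic variance is ignored.

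**1. What the paired test misses.** Clinic-mean change = −(1 − q)d; paired change = 0. With d = 0.5:
- q = 0.8: −0.2 × 0.5 = −0.10 SD
- q = 0.7: −0.3 × 0.5 = −0.15 SD
- q = 0.6: −0.4 × 0.5 = −0.20 SD

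**2. Simulation of the same mechanism** (4,000 runs per setting, N = 100, r = 0.6, d = 0.5, test level 0.05):

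| New staff | Pairs | Paired mean change | All-respondent mean change | Paired t rejects | Rank-sum on all rejects |
|---|---|---|---|---|---|
| 10% | 90 | 0.001 | −0.050 | 5.1% | 0.9% |
| 20% | 80 | 0.000 | −0.100 | 5.4% | 3.5% |
| 30% | 70 | −0.003 | −0.151 | 5.6% | 11.3% |
| 40% | 60 | 0.000 | −0.202 | 5.5% | 22.8% |

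The paired test rejects at about its nominal rate throughout. The rank-sum test responds to the fall, but it ignores the stayers' pairing and is conservative when turnover is low. With d = 1.0 the all-respondent fall is 0.10 to 0.40 SD, the paired test still rejects in about 5% of runs, and the rank-sum test in 2.5% to 77.8%.

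**3. Would a mixed model on all questionnaires repair this?** With a random worker effect and one time effect, the model weights stayers' changes against the joiner–leaver contrast by precision. In this scenario its estimate is −d(1 − q)(1 − r) / [1 − r(1 − q)]. At r = 0.5, d = 0.5:
- q = 0.8: −0.05 / 0.90 = −0.056, against a true −0.10
- q = 0.7: −0.075 / 0.85 = −0.088, against −0.15
- q = 0.6: −0.10 / 0.80 = −0.125, against −0.20

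It recovers only about 56% to 63% of the fall, so it does not estimate the clinic mean change.

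**4. Precision.** Variance of the paired change = 2s²(1 − r)/(qN). Variance of the all-respondent difference = 2s²(1 − qr)/N. The ratio, paired to all-respondent, is (1 − r)/[q(1 − qr)]:
- r = 0.5: 0.5/(0.8 × 0.60) = 1.04; 0.5/(0.7 × 0.65) = 1.10; 0.5/(0.6 × 0.70) = 1.19
- r = 0.6, q = 0.8: 0.4/(0.8 × 0.52) = 0.96
- r = 0.7: 0.3/(0.8 × 0.44) = 0.85; 0.3/(0.7 × 0.51) = 0.84; 0.3/(0.6 × 0.58) = 0.86

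The paired change is slightly less precise at moderate correlation and more precise at high correlation.

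**The case against.** The strongest reply has five parts.

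- **The decline would be visible.** A reader might infer that a fall brought by new staff must stay hidden. The article does not support that. The sentence before the test plans summaries at both times without restriction to paired workers, and a lower end-of-period mean would appear there. What stands is that the paired test would not detect it.
- **The plan is not purely paired.** The rank-sum test, taken literally, includes leavers and joiners. This is correct, but it leaves the population open. Substituting the signed-rank test would mend the naming and keep the restriction to stayers.
- **Clinic-level maintenance does not rest on this test.** The text defines it as the "extent to which blood pressure continues to be assessed after the active intervention period ends based on medical chart reviews", and those visits include ones handled by new staff. So it would be wrong to say that clinic-level maintenance as a whole would be misjudged. Normalization is nonetheless a separately named component with its own instrument, and charts show whether pressure was recorded, not how staff regard the practice.
- **The inputs are assumed.** This stands. The article gives no turnover, and lower scores among joiners are conjecture: the Table 2 footnote has clinic staff continue all the strategies in maintenance, so joiners may still be trained.
- **Respondents with one questionnaire are a matter for the analysis plan.** This is fair for the detailed handling. But the article itself names the tests, and those two tests imply different populations.

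**Conclusion.** The concern holds in a limited form. The first-named test addresses change among workers present at both times, while Table 3 places normalization at clinic level. The bracketed alternative addresses all respondents, and the article does not say which is meant. If 20–40% of end-of-period staff are new and score 0.5 SD lower, a clinic-level fall of 0.10–0.20 SD would leave the paired result at zero. With little turnover, or joiners who score like stayers, the effect is negligible.

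A reader might also infer that dropping unpaired questionnaires always widens the interval. It does not: against the all-respondent difference, the paired variance is 1.04 to 1.19 times as large at r = 0.5 but smaller at r = 0.7. The case for change is about what is estimated, not about precision. The outcome is secondary and neither co-primary analysis is affected, so the point is minor.

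**What to change.** State who the respondents are at each time, then:

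- Make the clinic-level normalization result the start-to-end difference in mean score over all completed questionnaires, for example by GEE with an independence working correlation. Standard errors should allow for repeated workers and, with only nine clinics, carry a small-sample correction.
- Report the stayers-only change as supporting, using a paired t-test or, if scores are skewed, the signed-rank test.
- Report the numbers of stayers, leavers and joiners.

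A mixed model with a random worker effect should not supply the clinic-level figure, for the reason shown in step 3 of the working.

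**Cost.** Analysis wording and a little more analysis work. No new data are needed if the end-of-period questionnaire goes to all staff in post; if it were sent only to those who completed the first, its distribution would have to change. The all-respondent difference can also be less precise than the paired change when within-worker correlation is high.
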